Using inclusion/ exclusion criteria potential participants will be identified through multiple general practices in North East and North Cumbria CRN. Five recruitment sites were pre-screened for feasibility by North East and North Cumbria CRN (through local CRN support), and two GP practices in North Tyneside Clinical Commissioning Group (CCG) provided feedback during the application for the study funding.

Recruitment will be organised in two stages: pre-screening and screening. The pre-screening stage will first identify potential participants from participating general practices (GPs), who have agreed to review their patient database using predetermined exclusion/ inclusion criteria provided by the study team. For those GP patients who meet the criteria, surgeries will post recruitment packs on the behalf of the research team. Recruitment packs include: an invitation letter from the GPs, a Participant Information Sheet providing information about the study, a cover letter from the research group, a reply slip where individuals can indicate if they are interested in hearing more about the study, and a pre paid return envelope. The pre-screening stage then invloves a researcher telephoning those individuals who have expressed an interest in hearing more about the study via the reply slip and answering any questions they may have. With their permission the researcher will also conducting a 5-item SARC-F questionnaire^31^  to assess safety to proceed in the study and evaluate the use of SARC-F as a pre-screening tool for the inclusion of older adults in community-based studies involving resistance exercise program. The SARC-F questionnaire has five components (0-2 points for each) that assesses any difficulties with the following: (i) strength; (ii) assistance with walking; (iii) rise from a chair; (iv) climbing stairs, and (v) falls in the last year (Appendix 1).

Individual assessed to be unsafe to proceed will be informed in detail why they are not eligible for the study, thanked for their time and asked about the possibility to take part in other studies conducted by the AGE Research Group led by [name] [name].

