Individuals assessed to be safe to proceed will be offered a home-based screening assessment, where possible this will be arranged at a day and time to suit potential particiapnts and their families if requested. This visit will be used to evaluate inclusion/ exclusion criteria not screened through general practices. The researcher will also measure participants’ grip strength and walking speed to evaluate their muscle strength and function based on the establish cut-offs (low grip strength: <20 kg in women, and <30 kg in men^5^; low walking speed: <0.8 m/s or ≥5 s over 4 m distance^5^). This information will serve two purposes: (i) for comparison with SARC-F results, and (ii) to allow equal distribution of those with some muscle strength weakness across intervention groups. For grip strength assessment, each participant will perform six trials (three in their right and three in their left hand, alternating between the hands), and the final grip strength value will be expressed as the maximum of the six trials. Each participant will complete walking speed assessment once.

The study aims to recruit 30 participants (15 men and 15 women) aged ≥65 years who meet the pre-screen and screening criteria. A reserve list of 6-9 eligible individuals will also be created to factor in replacement of those who withdraw early from the study.

**Randomisation** (main team member(s) responsible: [name])

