**Data collection**

- HOME-BASED SCREENING ASSESSMENT (main team member(s) responsible: [name])

Researchers trained in assessment with older adults will visit potential participants selected through general practices and pre-screened with the SARC-F (i.e. evaluated by the research team as safe to proceed) in their own home to carry out screening for other exclusion/ inclusion criteria not assessed at pre-screening (e.g. milk allergies, participation in structured resistance exercise in the last month). Grip strength and walking speed will be measured to establish participants’ muscle strength and function status based on the established cut-offs^5^. An informed consent will be conducted before the assessments. Eligible individuals will be informed about the study procedure and their journey through the study (from randomisation to post-intervention assessment). Non-eligible individuals will be explained why they did not qualify for the study, thanked for their time, and will be informed about the possibility to participate in other studies led by [name] [name] (AGE Research Group).

This visit with the informed consent will last about 35 (maximum 40) minutes.

- HOME-BASED BASELINE ASSESSMENT: HEALTH AND FUNCTIONING PROFILE (main team member(s) responsible: [name])

Trained researchers will visit 30 participants enrolled in the study in their own home to conduct in depth interview and baseline assessments of the following domains:

1. Sociodemographic profile: age; sex; marital status; education; social class, and multiple index of deprivation
2. General health and functioning: SF-12 Health Survey^29^; self-reported diseases diagnosed by a doctor; list of medication (prescribed and over-the-counter); Mini Mental State Examination; Geriatric Depression Scale (15-item version) and Barthel Index^30^ (Activities of Daily Living); blood pressure (systolic and diastolic)
3. Dietary intake: 24-hr dietary recall (Intake24 (https://intake24.co.uk/) multi-pass, computerised 24-hr recall supported by the Newcastle University)
4. Appetite assessment: a 4-item Simplified Nutritional Appetite Questionnaire^34^
5. Self-reported physical activity: questionnaire assessing the frequency and duration of low intensity, moderate intensity and vigorous intensity physical activity, as assessed in the Newcastle 85+ study^35^
6. Anthropometry: demi-span (sex-specific height calculation), waist, hip and calf circumference

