# Data analysis and statistical methods

The primary objectives of this pilot study are to assess the feasibility and acceptability of milk in combination with exercise as an intervention to improve muscle health in older adults aged ≥65 who may be at risk of developing sarcopenia in order to inform a main grant application. As such the sample size of this pilot study is limited to 30 participants and we do not make any claims of statistical power, especially for quantitative data. However, the data gathered will be explored for differences between the intervention and control group for the following quantitative measures after 6 weeks of intervention: physical performance, muscle strength, muscle mass, self-reported quality of life, and activities of daily living. We will evaluate the use of SARC-F tool for pre-screening of participants for whom is safe to be included in community-based intervention studies involving exercise. We will correlate data collected with SARC-F with the measures of muscle strength and function assessed at screen assessment. We will use descriptive and univariate/ multivariate statistical techniques in SPSS and Stata. Compliance with milk and control drink will be calculated as a percentage of actual consumption divided by expected consumption over the 6-week intervention. Calculations of the number of repetitions for each exercise within each RE session and the weight lifted will allow for calculation of several indices of training intensity. Participants’ experiences and views about the study will be also assessed with standardised open-ended questions. Data gathered form these questions will be analysed using qualitative analysis techniques, namely: content analysis. Content analysis involves the interpretation of the context of data whereby data is read and openly coded to break it down into emerging themes and sub-themes. A summary of the themes and sub-themes is then defined with the relevant quotations of the participant’s perspective. The research team includes extensive experience in both quantitative and qualitative data analysis.

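### The only analysis named for evaluating SARC-F is a correlation with grip strength and walking speed among people who passed the SARC-F telephone step; it cannot show whether the tool identifies who is safe to include

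*Protocol*

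**What the plan says.** In the Protocol's recruitment text (which follows the exclusion criteria), a researcher telephones people who returned the reply slip and administers SARC-F "to assess safety to proceed in the study and evaluate the use of SARC-F as a pre-screening tool" for community studies that involve resistance exercise. The scale is described: "The SARC-F questionnaire has five components (0-2 points for each"), which gives a total of 0 to 10, and Appendix 1 shows that higher means more difficulty. No total or item response is named as the point at which someone is unsafe.

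The call decides who goes further. "Individual assessed to be unsafe to proceed will be informed in detail why they are not eligible for the study", whereas "Individuals assessed to be safe to proceed will be offered a home-based screening assessment". Data collection repeats this: the home screening visit is for people "pre-screened with the SARC-F (i.e. evaluated by the research team as safe to proceed"). Grip strength and walking speed are first measured at that visit, partly "for comparison with SARC-F results" and partly to balance the groups.

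Data analysis and statistical methods then states the objective, "We will evaluate the use of SARC-F tool for pre-screening of participants for whom is safe to be included" in community exercise studies, and the analysis: "We will correlate data collected with SARC-F with the measures of muscle strength and function assessed at screen assessment".

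**The concern.** Two things do not fit together. First, the property to be evaluated is safety for inclusion, but the named analysis relates SARC-F to muscle strength and walking speed. These are measures of weakness, and a person can be weak and exercise safely, or strong and not. Second, the tool under evaluation helps to decide who receives the reference measurements. Nobody judged unsafe has grip or gait recorded, so the reject side of the screen is never verified, and the range of scores entering the correlation may be cut.

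At stake is what the pilot can say about SARC-F when the main study is planned. A weak correlation might be read as a poor tool when it partly reflects who was measured. A strong one might be read as support for the tool as a safety screen, which it would not be.

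**Working it through.** **Step 1: what can be estimated.** Cross the telephone decision with the reference result from the home visit.

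| Telephone decision | Below grip or gait cut-off | Not below |
|---|---|---|
| Judged unsafe | not measured | not measured |
| Judged safe | a | b |

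Sensitivity and specificity each need a cell from the first row. Only a/(a+b), the share of those passed who are weak, can be estimated. With adverse events in place of the cut-offs the table has the same gap, because people judged unsafe never exercise in the study. This step needs no assumption about a cut-off or pass rate.

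**Step 2: direction and possible size of attenuation.** The protocol gives no correlation, cut-off or pass rate, so there is no stated figure to reproduce. Assumptions: a normally distributed score, rejection of the highest scores only, a full-range absolute correlation r of 0.30, 0.40 or 0.50, and a passing share q of 50% to 95%.

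For truncation from above at c = Φ⁻¹(q), with λ = φ(c)/q, the ratio u of the restricted to the full standard deviation satisfies u² = 1 − cλ − λ². The correlation then observed is r′ = r·u / √(1 − r² + r²u²).

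Two worked cases with r = 0.40:
- q = 95%: u = 0.900, so r′ = 0.360 / √(0.84 + 0.16 × 0.81) = 0.366.
- q = 50%: c = 0, λ = 0.798, u = 0.603, so r′ = 0.241 / √(0.84 + 0.16 × 0.364) = 0.254.

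| Share passing | u | r = 0.30 | r = 0.40 | r = 0.50 |
|---|---|---|---|---|
| 95% | 0.900 | 0.272 | 0.366 | 0.461 |
| 80% | 0.764 | 0.233 | 0.316 | 0.403 |
| 50% | 0.603 | 0.186 | 0.254 | 0.329 |

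For r = 0.40 the relative loss runs from (0.400 − 0.366)/0.400 = 8.5% to (0.400 − 0.254)/0.400 = 36.5%.

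**Step 3: cross-check with a skewed 0–10 score.** A simulated right-skewed score (latent correlation 0.4, all inputs assumed) gave a full-range correlation of −0.36. The cut points below are arbitrary and serve only to vary the pass rate.

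| Scores kept | Share kept | Correlation | Share of weakest 10% on grip removed |
|---|---|---|---|
| below 8 | 97.6% | −0.341 | 8.6% |
| below 6 | 93.6% | −0.320 | 19.0% |
| below 4 | 83.2% | −0.281 | 38.8% |

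The relative loss runs from (0.360 − 0.341)/0.360 = 5.3% to (0.360 − 0.281)/0.360 = 21.9%.

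**Step 4: precision.** The number screened at home is not stated. Taking 30 randomised plus the upper reserve of 9 gives n = 39. It would be larger if people who fail other criteria at the visit are also counted. By Fisher's z, for r = 0.30: atanh(0.30) ± 1.96/√36 = 0.310 ± 0.327, that is, a 95% interval from −0.02 to 0.56.

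**The case against.** The protocol never promises sensitivity, specificity or diagnostic accuracy. It puts the evaluation and the correlation in separate sentences and does not say that the correlation is the whole evaluation. Adverse events, soreness and attrition are collected, and an analysis plan not seen here may bring them in. This has some force: the objective may be wider than the one analysis named. But no plan can supply grip and gait for people who were never visited, and the protocol as written links the safety objective to nothing else.

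The attenuation is also uncertain, and that stands in full. The gate is described as the research team's evaluation, which leaves room for judgement beyond a score. If almost nobody is judged unsafe, the loss is small, and at this sample size the sampling error in Step 4 is larger than most of the attenuation in Step 2.

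Two stronger readings are tempting. A reader might infer that the telephone step removes the people most at risk of sarcopenia. That high scorers are the ones rejected is plausible, since higher means more difficulty, but the protocol does not say so, and the removal shares in Step 3 rest wholly on assumed cut points. A reader might also infer that the trial therefore misses its target population. The protocol speaks only of people who may be at risk, its acceptability question names simply older adults living in the community, and it expects some enrolled participants to have weakness, which it balances between groups.

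Finally, evaluating SARC-F appears in neither the study aims nor the outcomes, and no claim of statistical power is made. No randomised comparison depends on this correlation.

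**Conclusion.** The concern holds in a limited form. The named correlation cannot support a conclusion about who is safe to include, and it cannot show whether the tool screens correctly, because it measures a different property and has no data on those rejected. Both follow from the protocol's text alone.

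The attenuation toward zero is conditional on high scorers being the ones rejected, and its size cannot be derived. The assumed scenarios span roughly 5% to 37% of the full-range value. The documents support neither a single figure nor a statement that the most at-risk people are removed. The point is secondary but worth correcting, because the pilot is meant to inform a larger study.

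**What to change.** Leave the safety gate as the investigators set it and change the claim and the reporting.

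1. In the recruitment text and in Data analysis and statistical methods, state that the correlation of SARC-F with grip strength and walking speed applies only to people who passed the telephone screen, and that it is not evidence on safety or screening accuracy.
2. Describe SARC-F score against adverse events, withdrawals and session completion in enrolled participants. Label this as descriptive and limited to those who passed: it has the same gap on the reject side, and 30 people allow no more.
3. Where the permission given by telephone covers it, report the distribution of SARC-F scores for everyone telephoned, with reasons for those judged unsafe. Readers can then see how much of the range was cut.
4. Report the proportion of enrolled participants below the grip or walking-speed cut-offs already given for the screening visit, and word conclusions about people who may be at risk of sarcopenia to match.

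The cost is mostly wording and a few tables from data already collected. Two downsides remain: the claim about SARC-F becomes weaker, and item 3 needs a check, because written consent is first taken at the home visit and people screened out by telephone have given only permission for the call.

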**Hypotheses**

1. Consumption of whole milk (2 × 500ml; 2 × ~20g protein) after a RE session twice a week over the period of 6 weeks post-randomisation is feasible as an intervention in older adults (aged ≥65) who may be at risk of sarcopenia.
2. The intervention is acceptable with good compliance, low attrition, and no adverse health effects, including appetite suppression, negative dietary changes, muscle damage and soreness.

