# Primary and secondary outcomes of the study

Primary outcome measures

1. Feasibility and acceptability of the intervention (Time frame: 6 weeks post-randomisation and baseline assessment).
2. Measures to include: applicability, dosage and duration of the intervention, compliance, attrition, and adverse health effects such as appetite suppression, dietary changes and muscle soreness (Time frame: 6 weeks post-intervention).

Secondary outcome measures for exploratory analyses

1. Difference in physical performance measures: Short Physical Performance Battery^26^ (balance, 4m-gait speed, 5-chair stands) (Time frame: at baseline and after 6 weeks of intervention).
2. Difference in muscle strength measure: maximum strength test^27^ (grip strength, GS; Jamar hand-held 5030J1 dynamometer) (Time frame: at baseline and after 6 weeks of intervention).
3. Difference in muscle mass measure: Bioelectric Impedance Analysis (BIA; Tanita MC-780MA Body Composition Analyzer) (Time frame: at baseline and after 6 weeks of intervention)^28^.
4. Difference in self-reported quality of life measure: SF-12 (Time frame: at baseline and after 6 weeks of intervention)^29^.
5. Difference in activities of daily living measure: Barthel Index^30^.

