There is also a small risk of gastrointestinal discomfort and possible unknown milk allergies (lactose or milk proteins). Participants who report any significant discomfort associated with milk or control drink intake (e.g. nausea, indigestion, diarrhoea, etc.) will be excluded from the study. In addition, there is a small risk of metabolic changes and weight gain due to the consumption of 650 kcal from whole milk and control drink (2 × week over 6 weeks) which will be counteracted by the increased energy expenditure during the RE programme. Appetite will be assessed at baseline and post-intervention, and total energy intake will be estimated using the Intake24 (computerised 24-hr dietary recall) pre- and post-intervention to examine any changes in energy intake. Also, weight and body fatness will be estimated using the Tanita Body Composition Analyzer at baseline and after the intervention.

There is also a small risk of falling during the walking test. However, the attending researcher will assess individual risk at the point of data collection (re-check exclusion criteria and endurance of consent) and omit measurements/ test if they felt it unsafe or that capacity to consent is not present or consent does not endure. It is made clear to participants that they are free to withdraw at any time. Should a decision to withdraw from the study be made, a reason for the withdrawal will be recorded. However, participants can withdraw without providing any explanation.

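### Excluding participants who cannot tolerate the drink, and replacing early withdrawals, can make acceptability, attrition and compliance look too favourable unless leavers are followed up and everyone allocated is counted

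*Protocol*

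**What the plan says.** The section on primary and secondary outcomes lists, among the feasibility and acceptability measures, "compliance, attrition, and adverse health effects such as appetite suppression, dietary changes and muscle soreness". The second hypothesis states the hoped-for result: "The intervention is acceptable with good compliance, low attrition, and no adverse health effects".

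Two rules act on the people these measures describe:

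- Recruitment (after the exclusion criteria): "A reserve list of 6-9 eligible individuals will also be created to factor in replacement of those who withdraw early from the study". The protocol does not define *early*, say whether replacement may follow allocation, or say how a reserve enters the minimisation.
- Ethical considerations and risk and burden: "Participants who report any significant discomfort associated with milk or control drink intake (e.g. nausea, indigestion, diarrhoea, etc.) will be excluded from the study". Stopping the drink is not distinguished from leaving follow-up.

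On data collection, the flow-diagram section and the post-intervention assessment section place participant feedback at the end of the post-intervention visit. Its themes include the volume and taste of the drink, changes in appetite and diet, and what participants disliked. Appetite and 24-hour dietary intake are remeasured at the last (12th) gym session.

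On analysis, the protocol says "Compliance with milk and control drink will be calculated as a percentage of actual consumption divided by expected consumption over the 6-week intervention". It gives no denominator for attrition, and it does not say how withdrawn, excluded or replaced participants enter compliance. It also says that "the sample size of this pilot study is limited to 30 participants and we do not make any claims of statistical power".

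**The concern.** Someone who develops nausea or diarrhoea from the drink is giving the most direct answer to the acceptability question. Under the ethics section that person leaves the study, and under the Recruitment section someone else may take the place. If the leaver then drops out of view, the outcome is partly measured on people selected for having had a good outcome.

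The pilot exists to inform a main grant application. A dropout rate that is too low, or an account of acceptability drawn from those who tolerated the drink, would carry straight into the design of that study.

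**Working it through.** The protocol states no attrition rate, threshold or power calculation, so there is no figure of its own to reproduce. The check has two parts.

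**1. What is collected from someone who leaves because of the drink**

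| Item | When collected | Available for a leaver? |
|---|---|---|
| Adverse events | Throughout, on the case report form | Yes, including the event that led to exclusion |
| Reason for withdrawal | At withdrawal | Yes, if the participant gives one |
| Muscle soreness | After each session and by evening call | Up to the point of leaving |
| Drink consumption | Supervised at the gym; log sheet and call for the home dose | Up to the point of leaving |
| Appetite, dietary intake | Baseline and 12th session | Baseline only |
| Feedback on the drink and study | End of the post-intervention visit | Not scheduled |

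The event survives, but the acceptability data do not. An analysis plan can choose denominators. It cannot analyse feedback that was never sought.

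**2. How much replacement could hide in the attrition figure**

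Inputs: 30 participants to be allocated (Randomisation section) and a reserve list of r = 6 to 9 (Recruitment section). Assumptions, chosen to show the extreme: the whole list is used after allocation, and nobody else leaves.

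Counting everyone allocated, attrition = r / (30 + r), with exact (Clopper-Pearson) 95% limits:

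- r = 6: 6/36 = 16.7% (6.4% to 32.8%)
- r = 9: 9/39 = 23.1% (11.1% to 39.3%)

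Counting only the final 30: 0/30 = 0%, with upper limit 1 − 0.025^(1/30) = 11.6%.

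If the reserves were spread evenly over the three arms (2 or 3 per arm), the per-arm figures would be 2/12 = 16.7% (2.1% to 48.4%) and 3/13 = 23.1% (5.0% to 53.8%). Reporting by arm will be imprecise.

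**3. The same effect on compliance (assumed values)**

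Expected intake per person is 2 × 500 ml × 2 sessions × 6 weeks = 12,000 ml. Suppose the final 30 take 95% of this and the leavers take between 0% and 50% of the same full volume. Neither value is in the protocol.

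- r = 6: (30 × 0.95 + 6 × 0)/36 = 79.2%, to (30 × 0.95 + 6 × 0.5)/36 = 87.5%
- r = 9: (30 × 0.95 + 9 × 0)/39 = 73.1%, to (30 × 0.95 + 9 × 0.5)/39 = 84.6%

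The final 30 alone would show 95%.

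**The case against.** The strongest reply is that nothing in the protocol removes replaced or excluded participants from the results. Attrition is a named outcome and reasons for withdrawal are recorded, so an exclusion for discomfort would ordinarily count as attrition and raise it. The 0/30 figure arises only if recorded withdrawals are set aside. Denominators are commonly left to a statistical analysis plan, which may exist. This stands: a reader might infer that the attrition and compliance results *are* biased, but the document supports only that they *can* be.

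A reader might also infer that every result will be based on 30. The text does not say so. Thirty is a recruitment and allocation target, and the only formula, for compliance, carries no number of participants.

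Replacement may also be meant only before the intervention begins, since the flow-diagram section aims to start it with 30 eligible, randomised participants. That is plausible, and the flow diagram itself is not shown. It does not wholly clear the point: the same section puts randomisation before a baseline phase of about 6 weeks, so a withdrawal in that interval already follows consent and allocation. Replacement before allocation would be harmless, but the protocol does not limit it to that.

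Adverse-event counts are little affected, because all events go on the case report form. It is also tempting to say that a single compliance percentage hides poor intake of the home dose. The two doses are observed separately and nothing prevents separate reporting, so that is a reporting choice.

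Finally, the exclusion rule is a safety measure in a pilot that makes no power claim. Whether someone with discomfort should continue the drink is a clinical decision and is not questioned here. None of these replies answers the loss of end-of-study feedback, appetite and diet data.

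**Conclusion.** The point holds in a limited form, as an inexpensive improvement to the protocol rather than a fault that invalidates the pilot.

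The firm part is data collection. As written, participants excluded for drink-related discomfort are not scheduled to give the feedback or the final appetite and diet measures on which acceptability rests. Those data would come mainly from people who tolerated the drink. This depends on no assumption about denominators.

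The conditional part is attrition and compliance. Full use of the reserve list after allocation, with no other losses, would mean 17% to 23% attrition reading as 0% if only the final 30 were counted. That is the extreme case. If everyone allocated is counted, or replacement occurs only before allocation, replacement does not bias post-allocation attrition. The compliance ranges are illustrations on assumed intakes.

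**What to change.** **Ethical considerations section.** Separate stopping the study drink, a decision left to the investigators as now, from leaving the study. Invite those who stop or withdraw, where their consent endures, to the post-intervention assessment and feedback, or to a short exit version that includes the appetite and diet questions. Count drink-related stops as intolerance events.

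**Recruitment and Randomisation sections.** Define early withdrawal and state whether replacement may follow allocation. If it may, treat reserves as additional participants allocated by the minimisation.

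**Data analysis section.** Report attrition, compliance and adverse effects by arm for everyone allocated, including those replaced. State how a leaver's expected consumption is defined; how to score it is a reporting choice, but it should be fixed in advance.

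**Cost.** A few sentences of wording and a small number of extra contacts: 6 to 9 if leavers number what the reserve list allows, each no longer than the 50-minute follow-up visit already planned. Some leavers will decline. The attrition and compliance figures may be less favourable, and per-arm intervals will be wide. The change needs to be in place before the first participant leaves, because feedback missed at exit may not be recoverable.
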